## Abstract

**Background:**

Liver transplantation is the only curative treatment for patients with end-stage liver disease. Short-term survival has improved due to improved surgical techniques and greater efficacy of immunosuppressive drugs. However, long-term survival has not improved to the same extent as the short-term survival, and the 10-year survival after liver transplantation is 60%. In addition to liver- and transplant-related causes, comorbidities such as cardiovascular, pulmonary, renal, and metabolic diseases have emerged as leading causes of morbidity and mortality in liver transplant recipients. The objective of this study is to assess the burden of comorbidities and identify both liver- and transplant-related risk factors as well as traditional risk factors that contribute to the pathogenesis of comorbidity in liver transplant recipients.

**Methods/design:**

The Danish Comorbidity in Liver Transplant Recipients (DACOLT) study is an observational, longitudinal study. We aim to include all adult liver transplant recipients in Denmark (n = approx. 600). Participants will be matched by sex and age to controls from the Copenhagen General Population Study (CGPS) and the Copenhagen City Heart Study (CCHS). Physical and biological measures including blood pressure, ankle–brachial index, spirometry, exhaled nitric oxide, electrocardiogram, transthoracic echocardiography, computed tomography (CT) angiography of the heart, unenhanced CT of chest and abdomen and blood samples will be collected using uniform protocols in participants in DACOLT, CGPS, and CCHS. Blood samples will be collected and stored in a research biobank. Follow-up examinations at regular intervals up to 10 years of follow-up are planned.

**Discussion:**

There is no international consensus standard for optimal clinical care or monitoring of liver transplant recipients. This study will determine prevalence, incidence and risk factors for comorbidity in liver transplant recipients and may be used to provide evidence for guidelines on management, treatment and screening and thereby contribute to improvement of the long-term survival.

*Trial registration* ClinicalTrials.gov: NCT04777032; date of registration: March 02, 2021.

## Background

Liver transplantation is the only curative treatment for patients with end-stage liver disease. Improved surgical techniques and greater efficacy of immunosuppressive drugs to prevent rejection have improved the short-term survival of liver transplant recipients. According to the European Liver Transplant Registry the current 1-year survival rate in liver transplant recipients is 86% [1]. However, long-term survival has not improved to the same extent with 5- and 10-year survival rates of 74% and 60%, respectively [1], and efforts to improve the long-term survival are needed.

In addition to liver- and transplant related causes, cardiovascular, pulmonary, kidney, and metabolic diseases contribute to the increased morbidity and mortality in liver transplant recipients [2–4]. Further knowledge of prevalence, incidence and risk factors for development of comorbidity is needed to identify high-risk individuals, to develop to targeted interventions, and to improve survival.

Cardiovascular diseases (CVD) have emerged as a leading cause of morbidity and mortality in liver transplant recipients [5–7], but the magnitude is not well explored, and a systematic review described a highly variable incidence of 1–41% for CVD [8]. Few studies have included controls, but one study indicated a higher incidence of ECG abnormalities in liver transplant patients than in the background population [9]. However, whether liver transplantation is an independent risk factor for CVD is poorly elucidated, and large, prospective cohort studies are needed to provide further insight into the risk factors and mechanisms driving CVD in liver transplant recipients.

Pulmonary and respiratory diseases, including pulmonary hypertension and hepatopulmonary syndrome are frequently seen in liver transplant candidates prior to transplantation [10]. In the acute post-operative phase after liver transplantation, pulmonary complications are frequent and both infectious and non-infectious pulmonary diseases contribute to morbidity and mortality in the acute phase [11]. The extent to which pulmonary diseases contribute to morbidity beyond the acute phase and the impact on long-term survival is unknown.

Studies have shown that mortality related to renal diseases increases over time post-transplantation [2]. Thus, renal insufficiency may be an important risk factor for late post-transplant mortality in liver transplant recipients. The aetiology leading to post-transplant renal failure is multifactorial and include use of immunosuppressive medication, metabolic syndrome, diabetes, circulating immunocomplexes, and factors that contribute to hepatorenal syndrome [12]. Despite the use of renal-sparing immunosuppression protocols, renal insufficiency remains a concern [2].

Metabolic syndrome, obesity and diabetes are highly prevalent in liver transplant recipients [13]. In addition, the use of certain immunosuppressive medication may induce dyslipidaemia [14]. Non-alcoholic fatty liver disease (NAFLD) is a common liver disease and is considered the liver manifestation of the metabolic syndrome [15]. Patients with NAFLD have an increased risk of cardiovascular diseases, kidney diseases and liver fibrosis [16, 17]. Although these are common comorbidities with potential impact on quality of life, morbidity and mortality, there is limited knowledge about metabolic diseases in liver transplant recipients, and studies to determine the incidence and whether liver transplantation is an independent risk factor for metabolic syndrome are needed.

## Study objectives

The overall objective of this study is to determine the burden of comorbidities in liver transplant recipients and to examine whether this differs from the background population. Furthermore, we want to identify both liver- and transplant-related risk factors as well as traditional risk factors that contribute to the pathogenesis of comorbidity in liver transplant recipients.AIM 1: To determine the prevalence and incidence of cardiovascular, respiratory, renal and metabolic diseases in liver transplant recipients, and whether the prevalence and incidence of these comorbidities are different from that of the background population.AIM 2: To identify liver- and transplant-related risk factors and traditional risk factors that contribute to the pathogenesis of cardiovascular, respiratory, renal and metabolic diseases in liver transplanted recipients and study potential interactions between these.AIM 3: To describe the kinetics of cytokines, chemokines, immune cells, proteomics and metabolomics after liver transplantation and identify biomarkers that can identify liver transplant recipients at high risk of developing cardiovascular, respiratory, renal, and metabolic diseases.

## Methods/design

The DACOLT study is a non-interventional, observational, longitudinal study to be initiated in March 2021. The study aims to include all liver transplant recipients living in Denmark (n = 580) as well as all patients who will be liver transplanted from 01.03.2021 until 01.03.2033 (estimated n = 600). Controls will be included from the Copenhagen General Population Study (CGPS) and the Copenhagen City Heart Study (CCHS).

Liver transplant recipients and controls will have uniformly measured clinical data and information regarding risk factors. Clinically measured primary outcomes include (1) coronary CT angiography, cardiac structure and function determined by echocardiography and cardiac CT, and electrophysiological abnormalities determined by electrocardiogram (ECG), (2) dynamic lung function indices measured by spirometry, (3) estimated glomerular filtration rates, (4) diabetes and dyslipidaemia. Several other outcomes are measured. Table 1 provides a complete overview of all clinical and physical measurements, Table 2 of biochemical measures, and Table 3 an overview of the content of the questionnaires used in the study.

**Table 1 Tab1:** Clinical measurements and collection of biomaterials

Measurements	Description
Anthropometry	Height: Stadiometer without shoes Weight: Scale (Soehnle, Nassau, Germany) without shoes or heavy clothing Waist and hip circumference: Measuring tape (SECA, Birmingham, UK)
Ankle–brachial-index	Doppler (Sonotrax Basic A, Edan, San Diego, CA, U.S.)
Blood pressure	IntelliVue MP5SC (Philips, Amsterdam, Netherlands)
Electrocardiogram	Cardiosoft V6.73 (GE Healthcare, Buckinghamshire, UK)
Spirometry	EasyOne® ultrasonic spirometer (ndd Medical, Zürich, Switzerland)
eNO	NIOX VERO® (Aerocrine AB, Solna, Sweden)
CT scans	CT angiography, CACS, CT chest, CT upper abdomen. 320-detector MSCT (Canon Aquilion ONE, PRISM, Canon Medical Systems, Otawara, Japan)
Transthoracic echocardiography	Vivid 9 Ultrasound System (GE Healthcare, Horten Norway) M-mode, colour tissue doppler, conventional spectral doppler, 2D speckle tracking, 3-dimensional echocardiography
Biobank	PBMC, plasma, serum

*CACS* coronary artery calcium score, *CT* computed tomography, *MSCT* multi-slice computed tomography, *PBMC* peripheral blood mononuclear cell

**Table 2 Tab2:** Hematological and biochemical measurements

Measurements	Description
Hematology	Hemoglobin, hematocrit, leucocytes, differential count, thrombocytes, red cell dimensions, complement C3
Electrolytes and iron metabolism	Sodium, potassium, calcium, iron, magnesium, ferritin, transferrin, chloride
Liver/ organ related	Aspartate aminotransferase, alanine aminotransferase, alkaline phosphatase, bilirubin, gamma glutamyltransferase, albumin, antitrypsin, amylase, creatinine kinase, lactate dehydrogenase
Coagulation	Activated partial thromboplastin time, coagulation factor II + VII + X, D-dimer, fibrinogen
Lipids	Total cholesterol, remnant cholesterol, HDL cholesterol, LDL-cholesterol, triglycerides, adiponectin, lipoprotein, apolipoprotein A, B, and E
Metabolic	Non-fasting glucose, fasting-glucose, non-fasting insulin, pro-insulin, C-peptide, fasting-insulin, HbA1c, ethanol, hydrogen carbonate
Renal function	Creatinine, urea, uric acid, eGFR
Thyroid function	Thyroid stimulating hormone, free T3/T4
Immunology	Immunoglobulin A and E, rheumatoid factor IgM
Inflammation	High sensitivity C-reactive protein, immunoglobulin A and B, rheumatoid factor (IgM)

**Table 3 Tab3:** Overview and examples of variables recording for questionnaires

Variable	Examples
Large questionnaire regarding lifestyle and health	
Smoking	Current, previous and passive smoking. Cumulative pack-years, type, filters, e-cigarettes
Alcohol and drug use	Current and previous alcohol intake, intravenous drug use, cannabis
Environmental exposure	Occupational dusts, organic- and inorganic gasses, vapors, fumes
Demographics	Ethnicity, nationality, marital status, children
Socioeconomic status	Level of education, household income
Work	Employment, income, night-work
Diet	Meat intake, vegetable intake
Daily living	Physical activity, social support, sleeping, stress, sun exposure
Medication use	Prescription and doses
Gender, ethnicity	Ethnicity, place of birth
Perinatal/childhood events	Birthweight, delivery at term, breast feeding, respiratory tract infections
Family history of diseases	Acute myocardial infarction, stroke, asthma, COPD, hypertension, diabetes, cancer, depression
Questions for females	Pregnancies, menarche- and menopause age, abortions
Self-reported disease	Asthma, COPD, allergies, diabetes
Symptoms	Angina, dyspnea, cough, wheeze, sputum, reflux
Fracture Risk Assessment Tool (FRAX®)	
Risk factors for fractures	Previous fracture, parent fractured hip, glucocorticoid use, rheumatoid arthritis
Major Depression Inventory (MDI)	
Self-report mood questionnaire	Lack of energy, feeling restless, appetite changes, feeling less self-confident

*COPD* chronic obstructive pulmonary disease

### Follow-up examinations

The participants in the DACOLT study will be examined at inclusion and after 10 years with extensive questionnaires, eNO test, computed tomography (CT) scans and transthoracic echocardiography (TTE) as well as physical measurements, ECG, spirometry and blood samples. Furthermore, every second year, participants will be invited to participate in a less extensive examination including physical measurements, TTE, ECG, spirometry, blood samples and a smaller questionnaire (Fig. 1).

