#### Controls from the Copenhagen General Population Study and the Copenhagen City Heart Study

CGPS is an ongoing observational population study with more than 110,000 participants from the greater Copenhagen area. All residents in the greater Copenhagen area > 40 years and 25% of 20–40 years old are invited to participate in the study and in follow-up examinations every decade. A random sample of 10,000 participants aged ≥ 40 years had a contrast enhanced CT of the chest including CT angiography of the heart performed. Of these, 6500 had a contrast enhanced CT of the abdomen.

CCHS includes a random population sample included from the greater Copenhagen area. Health surveys have been repeated 5 times between 1976 and 2015. Almost 4500 participants were randomly selected for echocardiography in 2013–2015.

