### Planned statistical analyses

Descriptive statistical analyses will be used to assess demographics, risk factors, and physical measurements. Groups will be compared using t-test or Mann–Whitney U test for continuous data and χ2 tests or Fisher’s test for categorical data. The large cohort of controls permits each liver transplant recipients to be matched on age and sex with between 5 and 20 controls. In cross-sectional studies the prevalence of the respective diseases among liver transplant recipients will be compared to the prevalence among the control group using logistic regression adjusted for traditional and/or presumed risk factors. Likewise, numeric variables will be compared using linear regression adjusted for traditional and/or presumed risk factors. For prospective studies, Cox regression, Kaplan–Meier curves, log-rank test, and mixed effect models will be used. In general, missing data is expected to be low and multiple imputations are not likely to be required. Characteristics for loss to follow-up will be assessed.

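### Recipients are re-examined every two years and CGPS controls every ten, so a time-to-event comparison of visit-detected incidence would be biased towards excess risk in recipients unless it is confined to common examinations

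*Protocol article*

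**What the plan says.** Four parts of the protocol article bear on this.

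- **Study objectives, Aim 1** asks "whether the prevalence and incidence of these comorbidities are different from that of the background population". Methods/design lists clinically measured primary outcomes. Besides CT these are echocardiography, ECG, "dynamic lung function indices measured by spirometry", eGFR, diabetes and dyslipidaemia.
- **Follow-up examinations:** recipients have the full examination at inclusion and at 10 years. In between, "every second year, participants will be invited to participate in a less extensive examination including physical measurements, TTE, ECG, spirometry, blood samples". The Questionnaires section places the interim visits at 2, 4, 6 and 8 years. CT is done only at inclusion and 10 years.
- **Controls:** CGPS residents are "invited to participate in the study and in follow-up examinations every decade". For CCHS, "Health surveys have been repeated 5 times between 1976 and 2015", and the only control echocardiography described is this: "Almost 4500 participants were randomly selected for echocardiography in 2013–2015".
- **Planned statistical analyses:** "For prospective studies, Cox regression, Kaplan–Meier curves, log-rank test, and mixed effect models will be used".

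The article says that measurements follow uniform protocols in all three cohorts. That concerns how a measurement is taken, not how often. The limitations paragraph covers selection, geography, loss to follow-up and recall, but not unequal surveillance.

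**The concern.** An outcome found only at a study visit is dated by the visit schedule as well as by the disease. Recipients have five occasions in ten years on which to become a case; a CGPS control has one. Recipient cases are therefore dated earlier. A recipient who develops the condition and then dies or drops out before year 10 can still be counted, whereas a control in the same position cannot.

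Both effects push the hazard ratio above 1, the direction the study expects to see. Covariate adjustment cannot remove them, because examination frequency is determined by group. The study is meant to inform guidelines on screening and monitoring, so an artefact of monitoring frequency would matter.

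**Working it through.** **The plan's own figures.** The nearest stated figure for a visit-detected outcome is the power of 0.82 for ECG changes (540 against 5,400, 11% in controls, prevalence ratio 1.4, so 0.11 × 1.4 = 0.154). The normal approximation at two-sided 5% gives 0.838, or 0.822 with continuity correction. The atherosclerosis figure (0.575 against 0.50) gives 0.916, or 0.909 with correction, against 0.90 stated. The strain figure gives 0.9996 against 0.99. All three reproduce, and all are cross-sectional. The article gives no figure for incidence.

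**Inputs from the article.** Recipient visits at 2, 4, 6, 8 and 10 years; CGPS control visit at 10 years; 540 and 5,400 subjects; survival after transplantation of 86% at 1 year and 60% at 10 years. The implied death hazards are:
- from transplantation: −ln(0.60)/10 = 5.1% a year;
- after surviving the first year: −ln(0.60/0.86)/9 = 4.0% a year.

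The second suits the existing recipients who are past their first year.

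**Assumed inputs, not in the article.** True incidence of 0.5 to 5% a year, equal in both groups; control mortality of 1% a year; loss of 3% a year where used; events dated at the detecting visit.

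**The mechanism in expected counts, at 2% a year.**
- *No deaths.* The cumulative proportion at 10 years is 1 − e^(−0.2) = 18.1% in both groups. Of the recipients, 540 × (1 − e^(−0.16)) ≈ 80 are detected by year 8 and about 18 more at year 10. All 5,400 × 0.181 ≈ 979 control cases are dated at year 10.
- *Recipient mortality 5.1% a year.* Seen only at year 10, recipients would yield e^(−0.51) × 0.181 = 10.9% detected. Seen every two years, they yield the sum over k = 1 to 5 of (e^(−0.04(k−1)) − e^(−0.04k)) × e^(−0.102k) = 13.6%. The interim visits alone raise the detected proportion by a factor of about 1.25 (13.6/10.9) with no change in disease.

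**Simulation with a true hazard ratio of 1.** Tie handling matters, because every control event falls at year 10.

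With Efron ties:
- complete 10-year follow-up, no deaths, 0.5 to 2% a year: about 1.01 to 1.10;
- mortality 1% a year in both groups, 2% incidence: 1.15;
- mortality 5.1% against 1%: 1.30 to 1.35 at 2% incidence, and 1.45 to 1.47 at 4%;
- over recipient mortality of 4 to 5% and incidence of 2 to 4%: about 1.25 to 1.45.

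With Breslow ties the values are somewhat higher. The table gives the median hazard ratio over 200 runs, with the share of runs declaring a false excess at two-sided 5%:

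| Scenario | 0.5%/yr | 1%/yr | 2%/yr | 5%/yr |
|---|---|---|---|---|
| Complete 10 years, no deaths | 1.05 (6%) | 1.08 (8%) | 1.17 (32%) | 1.47 (100%) |
| Mortality 5.1% against 1% | 1.25 (22%) | 1.33 (42%) | 1.43 (78%) | 1.80 (100%) |
| 3%/yr loss in both groups | 1.18 (16%) | 1.21 (26%) | 1.33 (66%) | 1.67 (100%) |
| Follow-up spread over 2 to 12 years in both groups | 3.1 (92%) | 3.2 (99%) | 3.5 (100%) | 4.6 (100%) |

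In an analysis at 6 years no control could yet have a visit-detected event, so the ratio is unbounded. When both groups have the same schedule, the median is 0.96 to 1.04 in every scenario. Dating events at interval midpoints is not a general cure: it leaves 1.16 to 1.37 with 3% loss and more than 3 with staggered follow-up.

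**The case against.** The strongest reply is that the article does not commit to the biased analysis. It lists methods for prospective studies without saying which endpoints enter a recipient-versus-control Cox model or how events are dated. Cox regression also suits within-recipient risk-factor work under Aim 2 and registry-dated events, and event dating is often left to an analysis plan. This stands in part. A reader might infer that the study will report a spurious excess; the text supports only an unaddressed risk. It remains a point about this document, because the unequal schedules, the incidence contrast and the methods are all fixed here and nothing reconciles them.

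Three further limits stand.

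- **Size.** It depends on assumed incidence and mortality. For outcomes of 1% a year or less, with complete follow-up and no deaths, the bias is close to negligible. The 5.1% death hazard is counted from transplantation and is too high for recipients past their first year. More visits also give more chances of a false positive, but the article gives no error rate, so no figure is attached to that.
- **Controls.** The ten-year interval is stated for CGPS only; for CCHS it is an inference from five surveys between 1976 and 2015. A reader might conclude that no incident echocardiographic outcome can exist in controls. The article only describes no repeat after 2013–2015, and the figure summarising data collection is not available here.
- **Registries.** It is tempting to treat registry diagnoses and prescriptions as neutral. Under Other data sources, recipients have annual routine examinations with blood samples, so diabetes, dyslipidaemia and renal disease are more readily picked up in them there too.

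**Conclusion.** The concern holds for one contrast: visit-detected binary incidence in recipients against controls, analysed by detection date. There the bias is upward in every scenario examined and vanishes when the schedules match. With equal true hazards, the expected hazard ratio (Efron ties) is about 1.01 to 1.10 at 0.5 to 2% annual incidence in the most favourable case. It is about 1.25 to 1.45 at 2 to 4% once recipient mortality of 4 to 5% a year is set against an assumed 1% in controls. It is larger when follow-up falls short of ten years, which is plausible with new transplants entering until 2033. Incidence and control mortality are assumptions; recipient mortality derives from the survival rates in the Background.

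It would be wrong to extend this to the whole study. The prevalence comparisons and all the power calculations are cross-sectional. CT is done in recipients only at inclusion and 10 years. Mixed models of continuous eGFR, lung function or strain do not depend on a detection date. None of these is affected by this mechanism. The point should be fixed, but it does not invalidate the design.

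**What to change.** Add to Planned statistical analyses, for recipient-versus-control incidence:

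1. For visit-detected outcomes, use only the examinations common to both groups (baseline and 10 years). Analyse them either as binary change or with an interval-censored model that respects each group's visit times. In both cases account for death before year 10, since matching the visits does not by itself deal with differential mortality.
2. Reserve the 2-, 4-, 6- and 8-year visits for within-recipient analyses.
3. For time-to-event contrasts with controls, use deaths and clinically overt hospital events from the registries, after confirming that the controls are linked in the same way. Treat registry diagnoses and prescriptions for diabetes, dyslipidaemia and renal disease as still open to surveillance bias, and say so when reporting them.
4. Limit the echocardiographic comparison with controls to baseline unless a repeat control examination exists.
5. Name differential surveillance among the limitations.

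The cost is wording, plus some loss of time resolution in the control contrast. No additional study visits are needed.
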